### Economic analysis

The cost of abdominal massage and optimal bowel care relative to optimised bowel care alone in people with MS who have NBD will be considered from NHS and societal perspectives. Health care resource use by patients in both trial arms will be collected at each of the follow-up time periods (i.e. weeks 1–6, 12, 18 and 24). This will include contact with health professionals and medications prescribed. These will be costed using NHS pay and prices or, where appropriate, using other (e.g. market-based) sources. Health-related quality of life will be assessed using the EQ-5DL questionnaire completed by all patients at baseline, at 6 weeks and at 24 week follow-up. QALYs associated with each arm of the trial will be calculated using the UK tariff scores (utility values) from the EQ-5DL descriptive system [23, 24].

Data on intervention costs and patient resource use will be aggregated and the statistical significance of differences in cost per patient between trial arms assessed by appropriate methods depending on the distributional characteristics of the data. Depending on the outcome measure, which would be QALYs, NBDS or both, if there is no statistically significant evidence that one treatment strategy is more effective than another, a cost-minimisation framework will be used, and the less expensive form of care will be recommended. If one strategy appears to be dominant (i.e. to be more effective and less costly than the alternative), the uptake will be recommended. If one form of care appears to be more effective and more expensive than the comparator, estimates of incremental cost-effectiveness (and cost-utility) ratios will be generated.

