**Methods/design:**

This is a multi-centred patient randomised superiority trial comparing an experimental strategy of once daily abdominal massage for 6 weeks against a control strategy of no massage in people with MS who have stated that their constipation is bothersome. The primary outcome is the Neurogenic Bowel Dysfunction Score at 24 weeks. Both groups will receive optimised advice plus the MS Society booklet on bowel management in MS, and will continue to receive usual care.

Participants and their clinicians will not be blinded to the allocated intervention. Outcome measures are primarily self-reported and submitted anonymously. Central trial staff who will manage and analyse the trial data will be unaware of participant allocations. Analysis will follow intention-to-treat principles.

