### Economic outcomes

The cost and use of NHS services will be collected via a ‘Patient resource questionnaire’. The cost to the patients and their families/carers will also be collected via the Patient resource questionnaire). From this information we will calculate the incremental costs, QALYs and incremental cost per QALY.

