### Statistical methods

#### Sample size calculation

The only published data available on the NBDS to inform sample size calculations is from our own pilot trial in the MS population [6]. Based on these data a sample size of 60 per group was calculated as necessary to detect a difference between groups of 4.21 (standard deviation, SD 7.02) at a 5% level of significance with 90% power. Thus for a fully powered study the sample size, allowing for a 20% drop-out, is 150. However, it was suggested by the funder that this figure be reviewed and increased. Therefore we have increased our sample size to 200 (100 per group), which would allow for greater than expected attrition.

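### The economic plan turns a non-significant effectiveness test into cost-minimisation and a recommendation of the cheaper care, although a superiority trial cannot show equal effects in this way

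*Protocol article*

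**What the plan says.** The abstract describes the design: "This is a multi-centred patient randomised superiority trial". The sample size section powers it for one purpose, to detect 4.21 NBDS points with an SD of 7.02.

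The economic analysis section of the protocol article then sets out a decision rule with three branches:

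- **No significant effect.** "if there is no statistically significant evidence that one treatment strategy is more effective than another, a cost-minimisation framework will be used". The same sentence goes on to fix what follows for practice: "and the less expensive form of care will be recommended".
- **One arm dominant**, that is, more effective and less costly. Its uptake is recommended.
- **One arm more effective and more costly.** Here "estimates of incremental cost-effectiveness (and cost-utility) ratios will be generated".

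The outcome that drives the rule is left open: "Depending on the outcome measure, which would be QALYs, NBDS or both".

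The economic outcomes section is unconditional: "From this information we will calculate the incremental costs, QALYs and incremental cost per QALY". The article gives no equivalence margin, no confidence-interval criterion for equal effect, and no QALY effect size or SD.

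**The concern.** Cost-minimisation compares costs alone, which is legitimate only when effects can be taken as equal. The first branch takes them as equal because a superiority test failed. Failure to reject may mean that there is no effect, or that a worthwhile effect was estimated too imprecisely. The rule does not separate the two.

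Two further problems come with it. Ratios appear in only one branch of the rule, whereas the economic outcomes section promises incremental cost per QALY in every case. And if NBDS is significant while QALYs are not, or the reverse, the article does not say which branch applies.

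Cost-effectiveness at 24 weeks is part of the stated hypothesis and of the first objective. The rule would therefore decide a headline conclusion, and it could do so without regard to the estimated QALY difference or to the joint uncertainty of costs and effects.

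**Working it through.** **Inputs from the article:** difference 4.21, SD 7.02, two-sided 5% level, 90% power, 60 per group required, 20% drop-out, 200 randomised (100 per group).

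**1. The plan's own figure.** The normal approximation gives n = 2 × (7.02 × (1.960 + 1.282) / 4.21)², which rounds up to 59 per group. With the noncentral t distribution, 59 per group has power 0.898 and 60 has 0.903, so 60 is right. Then 120 / 0.8 = 150. The sample size reproduces and is not in question.

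**2. What a just non-significant NBDS result leaves open.** SE = 7.02 × √(2/n) and half-width = t × SE. An estimate equal to the half-width has a 95% interval from 0 to twice the half-width.

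| Analysed per arm | SE | t | Half-width | Upper limit |
|---|---|---|---|---|
| 60 (number required) | 1.282 | 1.980 | 2.54 | 5.08 |
| 80 (100 less 20%) | 1.110 | 1.975 | 2.19 | 4.38 |
| 100 (no loss) | 0.993 | 1.972 | 1.96 | 3.92 |

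At 60 and 80 per arm the interval contains 4.21. At 100 it does not, but it still reaches nearly 4 points. Baseline adjustment with an assumed correlation r multiplies the limits by √(1 − r²). At r = 0.5 (factor 0.866) they become 4.40, 3.80 and 3.39, so only the first still contains 4.21.

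**3. How often the rule would fire on NBDS.** P(non-significant) = 1 − two-sided t-test power. For the adjusted columns, SD = 7.02 × √(1 − r²), which is 6.08 at r = 0.5 and 5.01 at r = 0.7. The correlations are assumptions, because the article gives none.

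| Analysed per arm | True 4.21, unadjusted | True 2.105, unadjusted | True 2.105, r = 0.5 | True 2.105, r = 0.7 |
|---|---|---|---|---|
| 60 | 10% | 63% | 53% | 37% |
| 80 | 3-4% | 53% | 41% | 25% |
| 100 | 1% | 44% | 32% | 16% |

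**4. QALYs, as illustration only.** The article gives no QALY inputs, so everything here apart from the EQ-5D time points is assumed. With utility measured at 0, 6 and 24 weeks, the area under the curve is (3/52)u₀ + (12/52)u₆ + (9/52)u₂₄. A utility gain of 0.03 from week 6 gives 0.03 × 21/52 = 0.012 QALY. With utility SD 0.20-0.30 and a common correlation of 0.6-0.8 between time points, the baseline-adjusted QALY SD is 0.041-0.081. At 60-80 per arm the rule would then fire in about 55-87% of trials. The result depends heavily on the assumed gain: 0.01 gives 91-94%, and 0.05 gives 13-73%.

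**The case against.** The strongest reply is that the trial is well powered for the effect it was designed to find. If massage lowers NBDS by 4.21 points, the rule misfires in 10% of trials at most, and less often with the planned baseline adjustment. That stands. The NBDS problem lies in smaller true effects, and the unadjusted 44-63% is an upper range that adjustment may bring down to 16-53%. Sixty analysed per arm would also mean 40% loss from 200, twice the planned figure.

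A reader might infer that the rule simply rejects massage whenever p exceeds 0.05, because massage is added to the control care. The documents do not support that. Costs include professional contacts and medication to week 24 from NHS and societal perspectives, both arms have the same amount of professional contact, and the background cites £1729 as the average cost of a constipation admission. Which arm will be cheaper is not known.

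A reader might also infer that QALYs will not be estimated after a null result. The economic outcomes section says that they will be. What the rule fixes is the recommendation, and the two sections disagree about whether a ratio is then produced.

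Finally, the bootstrap, acceptability curves and adjustment sets are details that an article may leave to a fuller document, so their absence is no fault. Nor is the wording of the dominance and ratio branches a separate error. The p-value trigger is different, because it is stated and not omitted.

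**Conclusion.** The point holds. As written, a non-significant superiority test is used as if it showed equal effectiveness, and a recommendation on care follows from it. Nothing else in the article repairs this, and the section on economic outcomes contradicts it.

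For NBDS the size depends on the true effect. The misfire risk is about 1-10% at the full design difference and 44-63% at half of it, or 16-53% with baseline adjustment at an assumed correlation of 0.5-0.7. These figures take 7.02 as the SD of the 24-week score, which the article does not spell out. For QALYs no figure follows from the documents. The 55-87% is one illustration under a chosen gain and is not a property of this trial.

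The logical error does not depend on any of these probabilities. It leaves the primary NBDS analysis, its test and the sample size untouched, and bears on the economic conclusion alone.

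**What to change.** Delete the p-value trigger for cost-minimisation and the automatic recommendation of the cheaper arm. Whatever the p values, estimate incremental cost and incremental QALYs jointly, and report the incremental cost-effectiveness ratio or net monetary benefit with its uncertainty, for example by bootstrap and an acceptability curve. Give cost per NBDS point alongside. Bring the economic analysis section into line with the unconditional statement under economic outcomes, and state which outcome governs the conclusion if QALYs and NBDS disagree.

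Keeping cost-minimisation behind an equivalence margin would be possible, but this trial is poorly placed for a tight one. For a 95% interval within ± 2.105 points (an assumed margin, half the design difference), true difference 0 and 90% power, n = 2 × (7.02 × (1.960 + 1.645) / 2.105)², or 290 per arm before baseline adjustment, against 100 randomised.

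The cost is a change of wording and a little more analysis of the same data. No new data are needed. The change should be made before results by arm are known.

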### Adverse events

The AMBER trial involves treatments which are well established in clinical practice for individuals with MS who have bothersome constipation; therefore adverse events (AEs) (although these are unlikely) will be those observed in everyday practice associated with optimised bowel care and abdominal massage. Expected AEs arising from the treatments are noted below and thus will not be collected as AEs but noted in the weekly follow-up data collection.Increased flatulenceAbdominal crampsStomach rumblings/noisesLoose stool, which in some instances may lead to faecal incontinence.

All AEs and serious AEs will be assessed for seriousness, causality, severity and expectedness and will be reported to the relevant regulatory bodies.

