## Methods/design

### Study design

The present study is a multi-centred, RCT set in routine care settings comparing the effectiveness of an experimental strategy of once daily abdominal massage for 6 weeks against a control strategy of no massage in people with MS who have stated that their constipation is bothersome. An integral part of the project will be the process evaluation which will follow a mixed methods, longitudinal, case study design [9, 10]. In addition at one site only, anorectal physiology studies to determine mechanism will be conducted in consenting patients in both groups.

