### Intervention

#### Both trial arms

Both intervention and control groups will receive a 6-week intervention consisting of one outpatient consultation followed by weekly telephone calls to review adherence. Thus both groups will have the same amount of health professional contact. Both groups will receive what we have termed ‘optimised bowel care’. Often, in people with MS, bowel care is delivered in a haphazard fashion with little standardisation or guidelines for treatment. Optimised care (delivered to both groups) will include advice which will be reinforced by providing the Bowel Care Advice Leaflet of the MS Society.

The intervention and control groups will differ as described:Control group (optimised bowel care). During the outpatient appointment the participants’ existing routine bowel care will be reviewed and optimised. For example, dietary and fluid advice will be given as well as encouragement to be more active and use a better defaecation position.Intervention group (abdominal massage and optimised bowel care). In addition to optimised bowel care as described for the control group, the intervention researcher, who will have been trained in the massage, will teach the participant and/or their carer how to deliver the abdominal massage. This will include viewing a short study-specific DVD showing the massage being given to a patient and self-massage techniques, a study-specific abdominal massage training booklet as well as a demonstration of the technique on the participant. During the training the carer or participant will try the various strokes and will be able to ask questions. Possible adaptations to accommodate a participant’s disability will also be discussed. It is recommended that the abdominal massage be included as part of the participant’s usual bowel care regimen. Daily application was recommended in our pilot study in people with MS, and this was found to be acceptable with 80% adherence reported in the massage diary [6].

Both groups will have weekly telephone calls (lasting approximately 10 minutes; weeks 1–6) where they will discuss any changes/difficulties with bowel management. The intervention group participants will also discuss frequency of use and any problems in using abdominal massage.

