### End of study/discontinuation

The trial may be prematurely discontinued on the basis of new safety information or for other reasons given by the Data Monitoring and Ethics Committee (DMEC) and/or Trial Steering Committee (TSC), Sponsor, regulatory authority or ethics committee concerned. The end of the study is the last participant’s final 24 week follow-up.

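### Four expected symptoms are excluded from adverse event collection, in conflict with the sentence that follows, and have no described event-level route after week 6

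*Protocol article*

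**What the plan says.** The Adverse events section of the protocol article names four expected effects of the treatments: more flatulence, abdominal cramps, stomach noises, and loose stool that may lead to faecal incontinence. It says that these "thus will not be collected as AEs but noted in the weekly follow-up data collection". Directly after the list it says that "All AEs and serious AEs will be assessed for seriousness, causality, severity and expectedness" and will be reported to the regulatory bodies. It gives no time limit for that second statement.

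The only weekly follow-up described is under Both trial arms: "Both groups will have weekly telephone calls (lasting approximately 10 minutes; weeks 1–6"), "where they will discuss any changes/difficulties with bowel management". One topic is added for one arm: "The intervention group participants will also discuss frequency of use and any problems in using abdominal massage". The same section says of the consultation and calls: "Thus both groups will have the same amount of health professional contact".

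On timing, the Study design section describes the strategy under test as "once daily abdominal massage for 6 weeks". The End of study section says: "The end of the study is the last participant’s final 24 week follow-up".

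**The concern.** The listed symptoms are the unwanted effects that the authors themselves expect from the treatments. Taking them out of AE collection is a stated rule, not a detail left to another document, and it raises three difficulties.

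- An event that is not collected as an AE cannot be graded as one, yet the next statement promises grading of all AEs and serious AEs.
- The substitute route, the weekly follow-up, ends at week 6 as described, while the primary outcome is at week 24.
- The calls do not have quite the same content in the two arms.

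At stake is whether the trial can give a clean between-arm account of its most plausible unwanted effects. The Background describes faecal incontinence as devastating for patients, so one of the four is not trivial. The primary analysis is unaffected.

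**Working it through.** The plan gives no figure on this point, so the check sets the passages side by side, with one subtraction.

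**1. The two statements in the Adverse events section.** Three readings are possible.

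- *All AEs means all except the four.* The four are then never graded for seriousness, causality or severity. Assessing expectedness has less left to do, because events already judged expected were removed first. A listed event that meets a seriousness criterion is not clearly covered.
- *All AEs includes the four.* The exclusion is then contradicted.
- *The four are excluded unless serious.* The mention of serious AEs may be meant this way, but the text does not say so.

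The wording does not decide between these.

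**2. The time window.** The inputs are calls in weeks 1–6 (Both trial arms), a massage period of 6 weeks (Study design) and follow-up of 24 weeks (End of study).

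- Prescribed massage period covered by calls: 6 of 6 weeks.
- Follow-up after the last call: 24 − 6 = 18 weeks, that is weeks 7–24.

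Those later weeks matter to the extent that massage continues. The Intervention section recommends making massage part of the participant's usual bowel care, so continuation is possible, but no figure is given. Controls receive the massage training materials only at the end of follow-up, so a randomised comparison of these symptoms remains available up to week 24.

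**3. What is captured for each listed event.** The sources are Primary outcome measure, Secondary outcome measures and Data collection.

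| Listed event | Noted in calls, weeks 1–6 | Nearest measure after week 6 |
|---|---|---|
| Flatulence | yes | NBDS flatus item, week 24 |
| Loose stool, faecal incontinence | yes | diary stool type, week 23; NBDS incontinence frequency, week 24 |
| Abdominal cramps | yes | none by name; NBDS discomfort during defaecation and CSS pain are the closest |
| Stomach noises | yes | none by name |

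Two of the four have a late measure, taken around one time point, as an outcome item and not as an event. Two have no clear late equivalent. None of the four has a described event-level route in weeks 7–24. The resource questionnaires at weeks 12 and 18 are described as covering service contacts, medication and costs, not symptoms. The NBIS is a symptom and quality-of-life questionnaire given at all time points, but the article does not list its items, so it cannot be counted either way.

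**4. Elicitation by arm.** Both arms have the same number of calls and the same question on bowel management, and all four symptoms could be raised under it. The difference is one added topic in the massage arm. Under Blinding, neither participants nor those delivering the intervention are blinded. An extra prompt may therefore raise reporting in that arm. The documents do not allow the size of any such effect to be estimated.

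**The case against.** Much can be said for the plan. The exclusion covers four mild, foreseeable symptoms of a low-risk intervention. The calls span the whole prescribed massage period. The symptoms that overlap with bowel function are compared between arms with identical instruments at the end of follow-up. A symptom checklist, severity fields and a definition of serious events may well be in the full protocol or case report forms, and tabulation belongs in the analysis plan, so their absence from a condensed article is no fault.

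Most of this stands, and it rules out two stronger readings.

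- A reader might infer that harms of massage go unrecorded for 18/24 = 75% of follow-up. The documents do not support this. Only the four listed events are carved out, other AEs and serious AEs have no stated cut-off, and flatus, incontinence and stool type are measured again at week 23 or 24. The 75% is also calendar time, not time on prescribed massage.
- A reader might infer that symptoms are prompted in the massage arm only, so that the comparison must be biased against massage. The shared bowel-management question contradicts the first part. The second is a possibility, not a demonstrated result.

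The objection does not remove the conflict between the two statements, which is in the printed text. Nor does it supply an event-level route after week 6.

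**Conclusion.** The point holds in a limited form. The two statements in the Adverse events section cannot both apply to the listed events as worded, and the handling of a listed event that meets a seriousness criterion is left open. For all four listed events no event-level route is described in weeks 7–24. For cramps and stomach noises there is also no clear later outcome measure. The added call topic may make elicitation in weeks 1–6 somewhat unequal.

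This rests on two assumptions: that the weekly follow-up named in the Adverse events section is the telephone calls, since no other weekly contact by staff is described, and that some participants continue massage after week 6, which the plan permits but does not quantify. If few continue, the late gap matters less and the conflicting wording remains the main issue. The change is worth making, but the flaw does not threaten the primary outcome.

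**What to change.** 1. Reconcile the two statements in the Adverse events section so that they agree on which events are collected and graded, and state explicitly how a listed event that meets a seriousness criterion is handled.
2. Use one identical prompted checklist of the four symptoms, recording presence and severity, in both arms at each weekly call and on the forms already used at weeks 12, 18 and 24. Ask it before the massage-specific topic, so that the added discussion in one arm cannot shape the answers.
3. Tabulate the checklist results by arm, with the number of participants assessed at each time point.

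The cost is a minor amendment, a few lines on existing forms, one table and slight extra burden for participants. No new contact is needed. If follow-up has already closed on the dates given under Trial status, the first step and a by-arm table of symptoms noted in the calls are still possible. The report should then say that event-level data on these symptoms stop at week 6.
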